**Chemistry**

AST

ALT

Creatinine

CRP

ALP

Albumin

Total Bilirubin

B2-microglobulin

Γ-Glutamyl Transferase

LDH

**Hematology**

Hemoglobin

WBC count with differential

Platelets

### **7.3.5 Pregnancy**

If relevant, a urine pregnancy test will be administered at Visit 2 and Visit 3. The results must be reviewed prior to initiating study treatment at each visit.

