| Treatment Regimen:         | Subjects will receive re-boost immunizations of 1.2 mg Vacc-4x + 0.06 mg Leukine® (sargramostim, recombinant human Granulocyte Macrophage Colony Stimulating Factor [rhu-GM-CSF], adjuvant) at Visit 2 and 3 (15±2 days between the immunizations). At Visit 5, eligible subjects whose CD4 count is $\geq 350 \times 10^6/L$ and virally controlled are expected to discontinue ART and will be followed for an additional 16 weeks without ART (at Visit 9 recommencement of ART will be recommended).                                                                                                                                                                                                                                                                                                                                                                                                                                                                                                                                                                                                                                                                                                                                                                                                                                                                                                                                                                                                                                                                                                                                                                                                                                                                                                                                                                                                                                                                                                                                                                                                                                                                                                                                                                                                                                                                                                                                                                               |

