## **3 STUDY DESIGN**

### **3.1 Overall Study Design and Flow Chart**

The study is an open label, multicenter, follow-up, re-boosting study of subjects who previously completed the immunization regimen with Vacc-4x active and stopped ART (at Week 28) in the CT-BI Vacc-4x 2007/1 Study (EudraCT Number 2007-006302-13). No restart of ART is required. The subjects will be re-boosted with two immunizations (Visit 2 and Visit 3) of Vacc-4x, 1.2 mg peptides (12 mg/mL), with a 2 week interval between immunizations.

At Visit 5 ART medication (if being used) will be stopped in subjects whose CD4 count  $\geq 350 \times 10^6/\text{L}$ , for a 16 week period. At Week 29 ART will be restarted, according to the Investigator and subject's decision, and the subjects will be followed for an additional 8 weeks (End of Study; Visit 10).

DTH will be measured at Visit 2, and at Visit 4 (3 weeks after the second re-boosting immunization).

Viral load, CD4 and CD8 counts will be measured at all study visits. T-cell responses will be measured at Visits 2, 4, 6, 9 and 10 (End of Study) both by ELISPOT, T-cell proliferation assay and intracellular cytokine staining.

Vital signs and clinical laboratory tests will be done at all study visits.

Monitoring of AEs and concomitant medications will be done continuously from the time of signing ICF through the End of Study.

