| Adverse Events                                            | x                                       | x                    | x              | x    | x                   | x                         | x     | x     | x                     | x               |
| Concomitant Medications                                   | x                                       | x                    | x              | x    | x                   | x                         | x     | x     | x                     | x               |

a. Immunization for the DTH skin reaction is performed on day indicated; the test is evaluated 48 hours after immunization. This evaluation can be made by the subject, if properly trained.

b. Height only once at Screening.

c. Includes measurements of hemoglobin, CRP, WBC, platelets, creatinine, AST (SGOT), ALT (SGPT), LDH, ALP, γ-GT, albumin, total bilirubin, and β2-microglobulin.

d. Viral load will be quantified by HIV RNA copies/mL using PCR. CD4 and CD8 counts will be determined using flow cytometry.

e. T-cell response will be measured by ELISPOT as well as T-cell proliferative response assay and intracellular cytokine staining.

f. A urine pregnancy test will be administered and a negative test will be confirmed, prior to study drug administration.

g. If on ART subjects whose CD4 count is  $\geq 350 \times 10^6/L$  and virally controlled at Visit 5 are expected to stop ART.

h. Restart according to Investigator's/subject's decision.

i. Blood samples should be taken before immunization (re-boosting).

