### **4.3 Exclusion Criteria**

A subject will not be eligible for this study if any of the following criteria apply:

1. Reported AIDS-defining illness within the previous year.
2. Malignant disease.
3. On chronic treatment with immune-suppressive therapy.
4. Unacceptable values of the hematologic and clinical chemistry parameters, as judged by the Investigator, including creatinine values  $> 1.5 \times$  upper limit of normal (ULN), and AST, ALT and alkaline phosphatase (ALP) values  $> 2.5 \times$  ULN.
5. Concurrent chronic active infection such as viral hepatitis B or C or tuberculosis.
6. Pregnant or breastfeeding women.
7. Women of childbearing potential not using reliable and adequate contraceptive methods (defined as: use of oral, implanted, injectable, mechanical or barrier products for the prevention of pregnancy; practicing abstinence; sterile) during the  $28 \pm 2$  days re-boosting period including the DTH and for 2 weeks after the DTH test, or sexually active male subjects with partners of child bearing potential unwilling to practice effective contraception during the  $28 \pm 2$  days re-boosting period including the DTH and for 12 weeks after the DTH-test.
8. Current participation in other clinical therapeutic studies.
9. Incapability of compliance to treatment protocol, in the opinion of the Investigator.

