### **6.3.2.4 Visit 5**

This visit should be 84 ( $\pm 3$ ) days from Visit 2.

If on ART, the subject will be instructed to now stop ART if their CD4 count is  $\geq 350 \times 10^6/\text{L}$  and virally controlled (undetectable VL [ $<50$ copies] over a period of three months on a stable antiretroviral regimen with no more than one blip allowed). If the CD4 count is  $<350 \times 10^6/\text{L}$  and/or the virus is not controlled, the subject will be instructed to remain on ART. The instruction will be based on the results of CD4 count and viral load from this visit. As soon as possible when these

results are available, and at the latest within one week after this visit, the investigator will contact the subject by phone and tell the subject to stop ART, or not to stop ART. Stopping of ART will be done according to local guidelines and their current clinical judgment and based on the individual ART the subjects are receiving. Subjects will be instructed to write down the date(s) when stopping ART and take this information to the investigator at the next visit.

The Investigator needs to see the results from the blood sampling at Visit 5 before the subject can stop ART. The information to the subject that he/she can stop ART and instructions on how to do this can be made by telephone. It is important that the treatment interruption period has a full 16 week duration.

The following procedures will be performed:

- Review of concomitant medications and AEs.
- Physical examination including weight.
- Vital signs (blood pressure, heart rate).
- Clinical chemistry and hematology.
- Viral load, CD4 and CD8 counts.

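### The Visit 5 instruction to stop ART has no pregnancy check, nominally 69 days after the last scheduled test and 42 or 56 days after women's required contraception ends

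*Protocol*

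**What the plan says.** **Pregnancy testing.** Section 7.3.5 schedules the test at two visits: "If relevant, a urine pregnancy test will be administered at Visit 2 and Visit 3". The Table 1 schedule, the procedure lists for Visits 2 and 3, and Section 8.2 agree. Table 1 footnote f gives the purpose: "A urine pregnancy test will be administered and a negative test will be confirmed, prior to study drug administration". The procedure lists for Visits 4 to 10 contain no pregnancy test.

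**Contraception for women.** Section 4.3 requires it for the "re-boosting period including the DTH and for 2 weeks after the DTH test". The synopsis version of the same exclusion ends with the DTH test and omits the further two weeks.

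**The stop-ART rule.** It appears in four places:
- Synopsis, Treatment Regimen: eligible subjects above the CD4 threshold "and virally controlled are expected to discontinue ART".
- Section 3.1: "At Visit 5 ART medication (if being used) will be stopped in subjects whose CD4 count" is at or above the threshold.
- Table 1, footnote g: those above the threshold and "virally controlled at Visit 5 are expected to stop ART".
- Section 6.3.2.4: "The instruction will be based on the results of CD4 count and viral load from this visit". It then adds: "Stopping of ART will be done according to local guidelines and their current clinical judgment".

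**What happens if pregnancy is known.** Section 4.3 excludes pregnant women. Section 4.4 lists pregnancy as a ground for withdrawal. Section 8.2 requires notification within 24 hours and follow-up to the end of the pregnancy.

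**The concern.** The trial has two interventions: two immunizations, and then withdrawal of effective ART for 16 weeks. The protocol confirms that a woman is not pregnant before each immunization, but not before ART is withdrawn. By Visit 5 her last scheduled test is about ten weeks old, and for at least the last six of those weeks (nominally) the protocol has not required contraception.

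A woman who conceived in that interval and did not know it could meet the CD4 and viral-load criteria and be told, possibly by telephone, to stop ART. Section 1.6 reports that viral rebound was seen once subjects stopped ART, so the pregnancy would be exposed to rebound until someone recognised it. That runs against the protocol's own position, which excludes pregnant women and makes pregnancy a reason to withdraw.

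**Working it through.** **Inputs (days from Visit 2; Table 1 and Sections 6.3.2.2 to 6.3.2.4 and 6.3.3.4)**
- Visit 3, last pregnancy test: Day 15 ± 2, so 13 to 17.
- Visit 4, last DTH test: Day 28 ± 2, so 26 to 30.
- Visit 5, stop-ART decision: Day 84 ± 3, so 81 to 87.
- Stop instruction: at the latest one week after Visit 5, so no later than 87 + 7 = Day 94.
- Visit 9, restart recommended: Day 196.

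**The plan's own intervals**
- DTH to Visit 5: 84 − 28 = 56 days = 8 weeks, as the synopsis states.
- ART-free period: 196 − 84 = 112 days = 16 weeks, as stated throughout.

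**Last scheduled test to the ART stop**
- To Visit 5, nominal: 84 − 15 = 69 days. With visit windows: 81 − 17 = 64 to 87 − 13 = 74.
- To the instruction, allowing the extra week: 64 to 94 − 13 = 81 days.

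**End of women's required contraception to the ART stop**
- Section 4.3: ends at Day 28 + 14 = 42. To Visit 5: 84 − 42 = 42 days. To the instruction: 81 − 44 = 37 to 94 − 40 = 54.
- Synopsis: ends at Day 28. To Visit 5: 84 − 28 = 56 days. To the instruction: 81 − 30 = 51 to 94 − 26 = 68.
- The two texts differ by 42 − 28 = 14 days. Under either, the requirement ends well before Visit 5.

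**What Visit 5 could detect.** Its procedures are review of concomitant medications and adverse events, physical examination, vital signs, chemistry and hematology, and viral load with CD4 and CD8 counts. None is directed at pregnancy. Section 8.2 does not count pregnancy itself as an adverse event, and the sample questions in Section 8.1 do not ask about it. Detection would depend on the woman reporting it or on an incidental finding.

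**With a Visit 5 test.** The interval from last test to Visit 5 falls from 69 days to 0, and the result is at most 7 days old when the instruction is given.

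**The case against.** The existing tests serve their stated purpose: they clear subjects for study drug and are placed before both doses. A test before the ART interruption is an added safeguard, not the correction of a false statement.

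Other protections exist. Two of the four rule statements say subjects are expected to stop, and Section 6.3.2.4 refers to local guidelines and clinical judgment. Visit 5 includes an examination and adverse event review. Section 4.4 allows withdrawal, Section 1.6 allows ART to be restarted for other medical reasons, and nothing bars an investigator from testing. These points stand, and they narrow the exposure. They do not close the gap. The guideline and judgment sentence mainly governs how ART is stopped, and at most permits a check. Withdrawal and restart depend on the pregnancy being recognised.

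The group is also narrow: women of childbearing potential, on ART at Visit 5, meeting the stop criteria, pregnant and unaware of it. The protocol gives no sex split, so the number could be zero. That limits the weight of the point.

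A reader might go further in three ways that the document does not support:
- *That a woman known to be pregnant would be kept off ART.* Sections 1.6, 4.4 and 5.2.1 leave room to withdraw her and resume treatment.
- *That harm to a pregnancy is established here.* Section 1.6 documents viral rebound after stopping and says nothing about pregnancy outcome or transmission.
- *That the disagreement between the synopsis and Section 4.3 causes the gap.* Aligning them at the longer period would still leave 42 days.

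**Conclusion.** The point holds as a cheap patient-safety improvement. As written, the plan can lead to ART being stopped in a woman with an unrecognised pregnancy, because the stop instruction rests on CD4 count and viral load. By Visit 5 the last scheduled test is nominally 69 days old (64 to 81 days by the time of the instruction), and required contraception ended 42 or 56 days earlier.

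This assumes that sites follow the schedule as written and do not add a test of their own. The number of women concerned is unknown and may be very small within the 30 to 40 planned subjects. No endpoint or analysis is affected.

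The 112-day ART-free period also has no scheduled test and no contraception requirement for women. A reader might infer that the protocol must therefore mandate both throughout. That does not follow: it would mean 196 − 42 = 154 more days of required contraception than Section 4.3, or 196 − 28 = 168 more than the synopsis, and up to four further tests. Sponsors and ethics committees could reasonably differ on those burdens. The two-week mismatch between the synopsis and Section 4.3 is a separate, minor drafting inconsistency.

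**What to change.** **Main change.** In Sections 6.3.2.4, 7.3.5 and 8.2 and in Table 1 (the pregnancy-test row and its footnote), require a negative urine pregnancy test at Visit 5, before the instruction to stop ART, for women of childbearing potential who are on ART. The cost is an amendment and one extra urine test, of a kind already used in the trial, at a visit that already takes place. It adds no delay, because the instruction already waits for that visit's blood results.

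**Separate consistency note.** Bring the synopsis into line with Section 4.3 by adding the two weeks of contraception after the DTH test for women.

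**Optional, for the sponsor and ethics committee.** Consider contraception through the ART-free period and repeat urine tests at Visits 6 to 9 for women off ART. A Visit 5 test cannot detect conception after that date, so the question deserves an explicit decision, but the main change does not depend on it.

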## **8 ADVERSE EVENT MANAGEMENT**

### **8.1 Non-serious and Serious Adverse Events**

The Investigator is responsible for the detection and documentation of events meeting the criteria and definition of an AE or SAE as provided in this protocol (see below). All AEs and SAEs that occur from the time written informed consent is obtained until completion of the study at Visit 10 must be documented. Information to be collected includes the description, date and time of onset and stop, intensity, duration, causality, seriousness relationship, outcome and action taken ([Section 8.1.4](#)). Even if the AE is assessed by the Investigator as not reasonably attributable to study drug, its occurrence must be recorded in the source documents and reported on the CRF.

During each study visit, after the subject has had an opportunity to spontaneously mention any problems, the Investigator should inquire about the occurrence of AEs. The following are examples of open-ended questions that may be used to obtain this information:

- “How are you feeling?”
- “Have you had any medical problems since your last visit/assessment?”
- “Have you taken any new medicines, other than those given to you in this study, since your last visit/assessment?”

### 8.1.1 Definition of an Adverse Event

An AE is any untoward medical occurrence in a subject administered a pharmaceutical product that does not necessarily have a causal relationship with this treatment.

An AE can therefore be any unfavorable and unintended sign (including an abnormal laboratory finding, for example), symptom, or disease temporally associated with the use of a medicinal product, whether or not considered related to the medicinal product.

Examples of AEs include:

- Exacerbation of a pre-existing illness following the start of the study.
- Increase in frequency or intensity of a pre-existing episodic event or condition.
- Condition detected or diagnosed after study drug administration even though it may have been present prior to the start of the study.

An AE **does not** include:

- Medical or surgical procedure (e.g., surgery, endoscopy, tooth extraction, transfusion); the condition that leads to the procedure may be an AE.
- Day to day fluctuations of pre-existing diseases or conditions present or detected at the start of the study that do not worsen.
- Situations where an untoward medical occurrence has not occurred (e.g., hospitalizations for cosmetic or elective surgery, social and/or convenience admissions).
- The disease or disorder being studied or sign or symptom associated with the disease or disorder unless more severe than expected for the subject's condition.
- Overdose of either study drug or concurrent medication without any signs or symptoms.

### 8.1.2 Definition of a Serious Adverse Event

An SAE is any untoward medical occurrence that at any dose:

- Results in death.
- Is life-threatening.

*Note:* The term “life-threatening” in the definition of “serious” refers to an event in which the subject was at risk of death at the time of the event; it does not refer to an event which hypothetically might have caused death if it were more severe.

- Requires in hospitalization or prolongation of existing hospitalization.

*Note:* Complications that occur during hospitalization are AEs. If a complication prolongs hospitalization or fulfills any other serious criteria, the event is serious. Hospitalization for

elective treatment of a pre-existing condition that did not worsen from Baseline is not considered to be an AE.

- Results in persistent or significant disability/incapacity.

*Note:* The term disability means a substantial disruption of a person's ability to conduct normal life functions. This definition is not intended to include experiences of relatively minor medical significance such as uncomplicated headache, nausea, vomiting, diarrhea, influenza, or accidental trauma (i.e., sprained ankle) that may interfere or prevent everyday life functions but do not constitute a substantial disruption.

- Is a congenital anomaly/birth defect.
- Important medical events that may not be immediately life-threatening or result in death or hospitalization but may jeopardize the Subject or may require intervention to prevent one of the outcomes listed in the definition above should also usually be considered serious.

*Note:* Examples of such events are intensive treatment in an emergency room or at home for allergic bronchospasm, blood dyscrasias, or convulsions that do not result in hospitalization; or development of drug dependency or drug abuse.

### **8.1.3 Clinical Laboratory Abnormalities and Other Abnormal Assessments**

Laboratory abnormalities are usually not recorded as AEs or SAEs. All abnormal laboratory values judged to be at least possibly drug related or clinically significant abnormal laboratory results of any causality not associated with the disease under study must be repeated. The Investigator will exercise medical judgment in deciding whether abnormal laboratory values are clinically significant. In some cases, significant changes within the range of normal will require similar judgment by the Investigator.

Clinically significant abnormal laboratory values should not be listed on the AE page of the CRF unless clinical signs or symptoms are present. If an abnormal laboratory value or assessment is clearly related to a medically defined diagnosis or syndrome, the diagnosis or syndrome will be recorded on the AE page, not the individual laboratory values.

All clinically significant abnormal laboratory results or assessments will be followed until they resolve (return to normal or values before re-boost) or stabilize, or until they are judged by the Investigator to be no longer clinically significant.

### **8.1.4 Recording of Adverse Events and Serious Adverse Events**

From the point of signing the informed consent form (ICF) to the first re-boost (first administration of study treatment), any worsening of an existing or new medical condition must be recorded on the Medical History CRF page. Following administration of study medication up to the Visit 10 (End of Study), any worsening of an existing or new medical condition must be recorded as an AE on the CRF. The Investigator should review all documentation (e.g., hospital progress notes, laboratory, and diagnostic reports) relative to the event being reported. The Investigator will then record all relevant

information regarding an AE/SAE on the appropriate CRF page. The Investigator will evaluate AEs using the following guidelines:

- Description of event (if the event consists of a cluster of signs and symptoms, a diagnosis should be recorded [e.g., flu syndrome] rather than each sign and symptom).
- Onset date and time.
- Stop date and time.
- Intensity should be described according to the Division of AIDS Table for Grading Severity of Adult and Pediatric Adverse Events, Version 1.0 December 2004; Clarification August 2009 (Appendix 15.1) as Mild (Grade 1), Moderate (Grade 2), Severe (Grade 3), or Life threatening (Grade 4). Intensity is defined as one of the following:
  - Mild: transient or mild discomfort; no limitation in activity; no medical intervention/therapy required.
  - Moderate: mild to moderate limitation in activity- some assistance may be needed; no or minimal medical intervention/therapy required.
  - Severe: marked limitation in activity, some assistance usually required; medical intervention/therapy required; hospitalization is possible.
  - Life-threatening: extreme limitation in activity, significant assistance required; significant medical intervention/therapy required; hospitalization or hospice care probable.

It is important to distinguish between SAEs and severe AEs. Severity is a measure of intensity, whereas seriousness is defined by the criteria provided in [Section 8.1.2](#). An AE of severe intensity need not necessarily be considered serious. For example, a migraine headache that incapacitates a subject for many hours may be considered a severe AE, whereas a stroke that results in a limited degree of disability may be considered mild, but should be reported as an SAE. If any parameter within a record of an AE changes, a fresh record should be made in the CRF. For example, when the severity of the AE increases, the AE should be recorded as resolved at the existing severity level and re-entered into the CRF with a new start date reflecting the first date of the increased severity.

- Seriousness (see definition of an SAE, [Section 8.1.2](#)).

The Investigator must record whether or not the AE meets the definition of serious. If the event is serious, the Investigator must complete an SAE Report Form.

- Relationship to study drug.

The Investigator must make a causality assessment for all AEs and must decide whether there is a reasonable possibility that the AE may have been caused by the study drug. If there is any valid reason for suspecting that there is a causal relationship between the AE and the study drug, the AE should be judged “possibly related,” “probably related,” or “definitely related”

to study drug. Unless an AE can be excluded from causality, it must be judged “possibly related” to study drug rather than “not related” to study drug.

- **Definitely Related:** An AE is considered definitely related when there is clear evidence that the event was caused by test article use. A definitely related event has a strong temporal relationship and an alternative cause is unlikely (other possible contributing factors can be ruled out).
  - **Probably Related:** An AE is considered probably related when there is a reasonable possibility that the event is likely to have been caused by test article use. The AE has a timely relationship to the study procedure(s) and follows a known pattern of response, but a potential alternative cause may be present.
  - **Possibly Related:** An AE is considered possibly related when there is some evidence to suggest a causal relationship or when there is a reasonable possibility that the event might have been caused by test article use. Typically, the event occurs within a reasonable time after test article use. However, other factors may have also contributed to the event, such as the subject’s clinical condition or concomitant treatments.
  - **Not related/Unrelated:** An AE is considered not related or unrelated when the cause of the AE is known, and the event is in no way related to any aspect of test article use.
- Outcome.

Outcome of AEs should be recorded as resolved, resolved with sequel, not resolved, or fatal based on the status of the AE at discontinuation from the study. If an AE is not resolved at the time of discontinuation, the AE should be followed until it is resolved (returns to normal or Baseline values) or stabilized, or until it is judged by the Investigator to be no longer clinically significant.
  - Action taken.

None, required treatment, reduction of dose, or permanent discontinuation of study drug. *All applicable actions taken should be recorded.*

